## Abstract

**Background:**

Current hyponatraemia guidelines are divided on the use of tolvaptan in hospitalised patients with moderate to severe hyponatraemia, due to an uncertain risk-benefit ratio. We will conduct a randomised trial to test the hypothesis that early use of tolvaptan improves the rate of serum sodium correction and clinical outcomes compared with current standard first-line therapy, restriction of fluid intake, without increasing the risk of serum sodium overcorrection.

**Methods:**

We will enrol hospitalised patients with euvolaemic or hypervolaemic hyponatraemia and serum sodium of 115–130 mmol/L at Austin Health, a tertiary care centre in Melbourne, Australia. Participants will be randomised 1:1 to receive either tolvaptan (initial dose 7.5 mg) or fluid restriction (initial limit 1000 ml per 24 h), with titration of therapy based on serum sodium response according to a pre-determined protocol over a 72-h intervention period.

The primary endpoint will be the between-group change in serum sodium over time, from study day 1 to day 4. Secondary endpoints include serum sodium increment in the first 24 and 48 h, proportion of participants with normalised serum sodium, length of hospital stay, requirement for serum sodium re-lowering with intravenous dextrose or desmopressin, cognitive and functional measures (Confusion Assessment Method Short form, Timed Up and Go test, hyponatraemia symptom questionnaire), 30-day readmission rate, treatment satisfaction score and serum sodium 30 days after discharge. The trial will be overseen by an independent Data Safety Monitoring Board. Serum sodium will be monitored every 6–12 h throughout the study period, with pre-specified thresholds for commencing intravenous 5% dextrose if serum sodium rise targets are exceeded.

**Discussion:**

We seek to inform future international guidelines with high-quality data regarding the utility and safety of tolvaptan compared to standard therapy fluid restriction in patients with moderate-severe hyponatraemia in hospital. If tolvaptan use in this patient group is endorsed by our findings, we will have established an evidence-based framework for tolvaptan initiation and monitoring to guide its use.

**Trial registration:**

Australia and New Zealand Clinical Trials Registry ACTRN12619001683123. Registered on December 2 2019

**Supplementary Information:**

The online version contains supplementary material available at 10.1186/s13063-022-06237-5.

## Administrative information

Note: the numbers in curly brackets in this protocol refer to SPIRIT checklist item numbers. The order of the items has been modified to group similar items (see http://www.equator-network.org/reporting-guidelines/spirit-2013-statement-defining-standard-protocol-items-for-clinical-trials/).

## Introduction

### Background and rationale {6a}

Low serum sodium, known as hyponatraemia, is the most common electrolyte disorder, affecting 15–30% of acute hospital inpatients [1, 2]. Severe hyponatraemia can have serious acute complications due to cerebral oedema, and even mild to moderate hyponatraemia is associated with falls, delirium and increased length of hospital stay [3, 4]. Hyponatraemia at hospital admission is associated with increased inpatient mortality, though causation is not established [5, 6].

‘Severe’ hyponatraemia is defined by the presence of severe symptoms such as vomiting, seizure and reduced conscious state [7]. Biochemically, hyponatraemia can be classified as mild (Na 130–135 mmol/L), moderate (125–129 mmol/L) or profound (< 125 mmol/L) [7]. A critical consideration in the management of moderate-profound hyponatraemia of duration > 48 h (or unknown) is the need to avoid rapid correction which may lead to osmotic demyelination syndrome and permanent neurological disability. Guidelines recommended aiming to increase serum sodium by 5–8 mmol/L per day, and not to exceed 10 mmol/L per 24 h [7].

Current guideline-directed management of hyponatraemia is largely based on expert opinion and has limitations. Most cases of euvolaemic or hypervolaemic hyponatraemia are perpetuated by non-osmotic release of arginine vasopressin (AVP, also known as antidiuretic hormone (ADH)), causing water retention. This condition is known as syndrome of inappropriate antidiuresis (SIAD). Fluid restriction is the first-line treatment for patients with hyponatraemia who are not hypovolaemic [4, 7]. This treatment can be difficult to reliably administer because of the need for supervision, and for competing therapies requiring fluid administration. Fluid restriction is ineffective in approximately 50% of cases and may lead to reduced compliance and poor quality of life [8–10].

Tolvaptan is an oral vasopressin V2-receptor antagonist that blocks AVP action in the kidney, inducing a water diuresis to raise serum sodium concentration. The efficacy of tolvaptan versus placebo (without fluid restriction) was established in the SALT-1 and SALT-2 trials in patients with mild-to-moderate hyponatraemia (mean baseline serum sodium 129.0 (SD 4.1) mmol/L). The SALT trials did not enrol acutely hospitalised patients; rather, patients with chronic hyponatraemia were electively admitted for the purpose of trial initiation, and patients with serum sodium less than 120 mmol/L and neurological symptoms were excluded [11]. Tolvaptan was approved in the USA by the Food and Drug Administration in 2009 for treatment of clinically significant hypervolaemic or euvolaemic hyponatraemia, defined as serum sodium < 125 mmol/L, or hyponatraemia that is symptomatic and has resisted correction with fluid restriction [12, 13]. The sodium cut-off recommendation from the FDA approval is not clearly evidence-based and instead is based on expert opinion regarding which patients with hyponatraemia are likely to benefit from treatment in general [12].

Off-label experience with tolvaptan post-approval has identified benefits and risks. While the SALT trials reported excessively rapid correction of hyponatraemia (rise in sodium > 12 mmol in 24 h) in 1.7% of tolvaptan-treated patients (5.6% of an SIAD subgroup), observational studies of tolvaptan in moderate-to-profound hyponatraemia have shown highly variable rates of biochemical overcorrection in patients with initial serum Na < 125 mmol/L, ranging from 0 to 30% of cases [14–17]. An international hyponatraemia registry observed overcorrection of serum sodium in 12.1% of cases of tolvaptan use [9]. This experience has led some to recommend reduced initial dosing of tolvaptan (e.g. 7.5 mg) to improve its safety profile [18, 19]. At least one case of osmotic demyelination due to tolvaptan has been published, in a patient with decompensated cardiac failure in whom tolvaptan was inappropriately continued for several days despite a large initial rise in serum sodium [20, 21].

Currently, tolvaptan use in hospitalised patients with moderate to profound hyponatraemia is not evidence-based as there are no randomised controlled trials comparing the use of tolvaptan in hospitalised patients against standard of care fluid restriction. International guidelines are divided on the use of tolvaptan in hyponatraemia with lower sodium concentrations, due to concern regarding risk of sodium overcorrection [4, 7]. European guidelines recommend against the use of tolvaptan in moderate-profound hyponatraemia [7], whereas US/Irish guidelines acknowledge that there is insufficient evidence for tolvaptan use with serum sodium < 120 mmol/L, but endorse its use with appropriate monitoring of serum sodium levels, and prompt intervention if the recommended rate of serum sodium increase is exceeded [4]. Other potential concerns raised about tolvaptan include cost [22] and risk of liver function derangement seen with sustained higher-dose tolvaptan therapy for other indications (e.g. autosomal dominant polycystic kidney disease) [23].

Thus, there is a critical evidence gap with respect to efficacy and safety of tolvaptan in the very patients for whom it would be most useful. As such, there is physician reluctance to use what may be a safe and more efficacious therapy than fluid restriction if prescribed appropriately. There is an international need for rigorous randomised comparisons between tolvaptan and fluid restriction to determine evidence-based protocols for the use of tolvaptan in hospital inpatients with moderate to profound hyponatraemia, to clarify its role and ensure optimal patient outcomes.

### Objectives {7}

Aim: To compare the efficacy and safety of tolvaptan versus a rigorous, protocol-based fluid restriction to raise serum sodium levels in acute hospital inpatients with moderate-to-profound euvolaemic or hypervolaemic hyponatraemia.

Hypothesis: Tolvaptan will be more effective than fluid restriction in raising serum sodium and will lead to faster improvement in hyponatraemia-related symptoms, reduced length of hospital stay, without increasing adverse events.

### Trial design {8}

We will conduct a 3-day, parallel group, open-label, randomised, controlled trial of tolvaptan versus fluid restriction in hospitalised patients with moderate-to-profound hyponatraemia (Na 115–130 mmol/L). Patients will be randomised 1:1 to the tolvaptan or fluid restriction groups, with the intervention titrated daily based on serum sodium response according to a pre-determined protocol. The trial is designed to determine superiority. A 24–48h run-in period prior to randomisation will allow exclusion of patients with autocorrection of hyponatraemia due to an acutely reversible cause of non-osmotic AVP release.

## Methods: participants, interventions and outcomes

### Study setting {9}

We will enrol hospitalised patients with euvolaemic or hypervolaemic hyponatraemia, serum sodium 115–130 mmol/L at Austin Health, a tertiary care centre in Melbourne, Australia. Participants will be randomised 1:1 to receive either tolvaptan (initial dose 7.5 mg) or fluid restriction (initial limit 1000 ml per 24 h), with titration of therapy based on serum sodium response according to a pre-determined protocol over a 72-h intervention period.

### Eligibility criteria {10}

Inclusion criteria:
Serum sodium 115–130 mmol/L on direct sodium measurement (venous blood gas), corrected for glucose level if glucose > 10 mmol/L [24]Age 18 years or overInformed consent (patient, or medical treatment decision maker)

Exclusion criteria:
Hypovolaemia as defined as either:
Clinical impression of hypovolaemia; orUrine sodium < 20 mmol/L (or urine chloride < 10 mmol/L in the presence of metabolic alkalosis) in the absence of pitting oedema.Polydipsia/polyuria, defined by first collected urine sample specific gravity < 1.003Severe symptoms of hyponatraemia warranting hypertonic saline:Vomiting (not attributable to other cause)Coma, defined by GCS < 8 on day 1 of admissionDeep somnolence, defined by sedation score > 1 on day 1 of admissionSeizure at any time in admissionRespiratory arrest at any time in admissionThiazide or thiazide-like diuretic use within preceding 5 daysRisk factors for osmotic demyelination syndrome:
Malnutrition (BMI < 16 or other clinical concern)Alcohol abuse (> 14 standard drinks per week)Child-Pugh B or C CirrhosisHypokalaemia (≤ 3.0 mmol/L) on day 1, or need for intravenous potassium replacementIncrement in serum sodium from baseline to day 1 of > 0.5 mmol/L/h or > 10 mmol/L/24 hOther potential endocrine cause of hyponatraemia:
Untreated glucocorticoid deficiency or mineralocorticoid deficiency (evaluated with serum cortisol level, in context of clinical history and concurrent medications)Significant hypothyroidism (TSH > 20 IU/L, and/or free T4 < 6 pmol/L)Chronic kidney disease stage 5 (estimated glomerular filtration rate (eGFR) < 15 ml/min/1.73 m^2^ or renal replacement therapy)Systolic blood pressure < 100 mmHgInability to drink fluid unaidedPregnancy (by history, confirmed if necessary by serum *β*HCG) or breastfeedingMarked hyperglycaemia (day 1 venous blood gas glucose > 30 mmol/L)

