#### Intervention description {11a}

Tolvaptan or fluid restriction will be administered and titrated according to serum sodium response (Table 1). In the tolvaptan group, the initial dose will be 7.5 mg, and in the fluid restriction group, the initial total fluid restriction will be 1000 mL.

**Table 1 Tab1:** Dosing protocol for study interventions

DAY	Serum sodium	Prior 24 h sodium increment (mmol/L)	Tolvaptan (TOL) Group	Fluid Restriction (FR) Group	Sodium normalised protocol (both groups)
**1**	115–130		7.5 mg	1000 mL	
**2**	> 134	Any	➔	➔	1500 mL fluid restriction^a^
	≤134	> 8	Nil^b^	Nil^b^	
		5–8	7.5 mg	1000 mL	
		0–4	15 mg	750 mL	
		< 0	30 mg	500 mL	
**3**	> 134	Any	➔	➔	1500 mL fluid restriction^a^
	≤134	> 8	Nil^b^	Nil^b^	
		5–8	Same as D2	Same as D2	
		0–4	Dose increment^c^	FR increment^c^	
		< 0	Dose increment^c^	FR increment^c^	
**4**	Usual care after morning blood test including repeat serum sodium 30 days after discharge.				

^a^All participants regardless of group assignment with Na > 134 mmol/L on day 2 or on day 3 will receive a 1500-mL fluid restriction that day and no other intervention unless the Na increment was > 8 mmol/L over the preceding 24 h in which case they will not receive fluid restriction or tolvaptan

^b^Participants with Na increment > 8 mmol/L over the preceding 24 h will not receive a fluid restriction or tolvaptan for that day, regardless of group assignment

^c^Stepwise dose/fluid restriction increments:

• Tolvaptan: 7.5 mg ➔ 15 mg ➔ 30 mg ➔ 60 mg

• Fluid restriction: 1000 mL ➔ 750 mL ➔ 500 mL ➔ 0 mL

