Subsequent daily study visits will evaluate the change in serum sodium over the previous 24 h, reassess volume status and then determine the dosage of tolvaptan or the limit of fluid restriction for that study day, depending on allocation. Early morning bloods will facilitate morning decision-making. Participants whose sodium level increases at the desired rate 5–8 mmol/L over 24 h will continue the same dose of their intervention. Participants whose serum sodium rise is below target will have escalation of intervention—either tolvaptan dose increase (e.g. from 7.5 to 15 mg), or reduction of fluid restriction limit (e.g. 1000 to 750 mL). Participants with decreased serum sodium despite their initial intervention will have more rapid escalation of intervention dosing (e.g. tolvaptan from 7.5 to 30 mg; or fluid restriction from 1000 to 500 ml). Participants who record a 24-h serum sodium rise > 8 mmol/L (or have required intravenous dextrose due to Na > 8 mmol above target during the 24-h period) will not receive either tolvaptan or fluid restriction the following day. Participants who achieve normalisation of serum sodium concentration (135 mmol/L or above) during the course of the trial from either arm will default to a 1500 mL ‘maintenance’ fluid restriction, unless the rise in serum Na was > 8 mmol, in which case they will have free fluid intake.

Tolvaptan doses will be administered prior to 1200 (ideally prior to 1000) to allow safe monitoring of effect during daytime hours with serum sodium measurement 6 and 12 h post dose.

Direct sodium measurement from venous blood gas samples will be preferred to determine outcomes and treatment decisions, unless this is not available. In the setting of glucose levels > 10 mmol/L (> 180 m/dl), a correction factor will be applied according to the formula published by Hillier and colleagues in 1999 (Fig. 1) [24], as endorsed by the European hyponatraemia guidelines [7]. This formula adds 2.4 mmol/l to the measured serum sodium concentration for every 5.5 mmol/L (100 mg/dl) incremental rise in serum glucose. For glucose levels below 10, this amounts to correction by 1 mmol/L or less, therefore for we have chosen to implement this correction for glucose > 10 mmol/L only for practical purposes.

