#### Criteria for discontinuing or modifying allocated interventions {11b}

Overcorrection will be defined according to the European guidelines as an increment in plasma sodium of > 10 mmol/L in 24 h [7]. Overcorrection will be defined as a serious adverse event (SAE) and will prompt individualised management by the treating medical team in collaboration with the endocrinology consult service for decisions regarding re-lowering of plasma sodium with intravenous 5% dextrose therapy.

If the serum sodium rise has not exceeded 10 mmol/L in 24 h but is rising at a faster than desired rate, prophylactic intravenous 5% dextrose will be administered, per protocol. In the event that sodium concentration rises by > 6 mmol/L within 6 h of tolvaptan, or > 8 mmol/L within 12 h of tolvaptan administration, this will be initiated at a rate to match urine output, with increased frequency of sodium monitoring (Table 2) in accordance with safety advice issued by Otsuka Australia Pharmaceutical [28]. This infusion will be discontinued if the plasma sodium then falls back within the target range, and serial sodium monitoring will continue as standard protocol.

**Table 2 Tab2:** Thresholds for intervention with intravenous dextrose 5% in the context of sodium rise following tolvaptan dose

Rise in serum sodium	Time post-tolvaptan	Action
> 6 mmol/L	Within 6 h	Commence IV dextrose 5% at rate equivalent to urine output, continue to monitor frequently and cease when sodium back within target range
> 8 mmol/L	Within 12 h	
> 10 mmol/L	Within 24 h	Aim for re-lowering with bolus hypotonic fluid

In the event that daily bloods are not available for any reason, management will revert to a 1.5-L fluid restriction for both groups while awaiting further results.

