## Discussion

Tolvaptan has the potential to have great utility in the treatment of patients with moderate-to-profound hyponatraemia, but its uptake has been limited by lack of evidence for such patients. In additional, there are concerns regarding safety, level of benefit and potential cost. The absence of evidence is reflected in the divergent recommendations in current hyponatraemia guidelines [4, 7].

Hyponatraemia is a common clinical management problem, and until recently, the complexity and need for individualised therapy may have contributed to a lack of reliable evidence in this field.

Recent research has interrogated traditional management to provide an evidence base for fluid restriction in trial conditions and has reported limitations with this first line approach [26, 27]. Our study will provide a randomised comparison of tolvaptan and fluid restriction, which, despite observational trials and growing clinical experience, is yet to be formally evaluated [14–17].

Limitations of this study include its open-label design, necessary use of an unvalidated hyponatraemia symptom questionnaire, and single-centre operation. Another limitation common to all trials in hyponatraemia in hospital is that a proportion of patients with SIAD may improve spontaneously without, or despite, intervention, due to resolution of the underlying cause of non-osmotic vasopressin release. We are mitigating this issue by delaying recruitment at least 24–48 h after hyponatraemia is identified. Strengths of this trial include its prospective, randomised design, and a pre-specified protocol to reassess and titrate interventions daily, in keeping with clinical practice. Another strength is use of the increasingly recommended lower dose 7.5 mg of tolvaptan that has not been assessed in previous randomised trials.

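### A sodium rise of more than 8 and up to 10 mmol/L in the 24 h before day 1 does not hold back the first treatment, although the same rise on day 2 or 3 withholds both treatments

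*Protocol article*

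**What the plan says.** **Entry.** In Eligibility criteria {10}, under the risk factors for osmotic demyelination, a patient is excluded for an increment "in serum sodium from baseline to day 1 of > 0.5 mmol/L/h or > 10" mmol/L/24 h. The inclusion range is 115–130 mmol/L.

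**Day 1.** In Table 1 (Intervention description {11a}) the day-1 row gives 7.5 mg or 1000 mL at sodium 115–130 mmol/L. The cell for the prior 24 h increment is empty.

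**Days 2 and 3.** Both rows give no treatment in either arm when the increment exceeds 8 mmol/L. Footnote b reads "Participants with Na increment > 8 mmol/L over the preceding 24 h will not receive a fluid restriction or tolvaptan for that day". The text below the table agrees: after a 24 h rise above 8 mmol/L, participants "will not receive either tolvaptan or fluid restriction the following day". The rise that the protocol aims for is lower: "Participants whose sodium level increases at the desired rate 5–8 mmol/L over 24 h will continue the same dose of their intervention".

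**Run-in.** Trial design {8} says that a 24–48 h "run-in period prior to randomisation will allow exclusion of patients with autocorrection of hyponatraemia". The Discussion says of spontaneous improvement: "We are mitigating this issue by delaying recruitment at least 24–48 h after hyponatraemia is identified". Neither gives a numeric limit.

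**Later safeguards.** Section {11b} defines overcorrection as a rise above 10 mmol/L in 24 h and handles it as a serious adverse event, with a decision on re-lowering. Short of that, if sodium "but is rising at a faster than desired rate, prophylactic intravenous 5% dextrose will be administered, per protocol". The numeric triggers for this are in Table 2, captioned "Thresholds for intervention with intravenous dextrose 5% in the context of sodium rise following tolvaptan dose": above 6 mmol/L within 6 h, or above 8 mmol/L within 12 h.

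**The concern.** The protocol sets its own limit on how much a patient's sodium may have risen in 24 h before more treatment is given, and that limit is 8 mmol/L. It applies in both arms and stops fluid restriction as well as tolvaptan, so it works as a limit on the rise itself and not only on drug response. On day 1, when every participant is treated, the only numeric check is the looser entry limit of 10 mmol/L/24 h. No reason is given for the difference.

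The patients in the gap are already above the 5–8 mmol/L daily target when they get their first dose. All of them came from the range that the Background calls profound (below 125 mmol/L). The Background also names osmotic demyelination, with permanent neurological disability, as the reason to avoid fast correction. A rise of this size before any study treatment also resembles the autocorrection that the run-in is meant to screen out.

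**Working it through.** The plan gives no figure to reproduce. The check compares two stated limits and asks whether any other rule closes the gap between them. I read the entry limit as applying to the 24 h before day 1. Statistical methods {20a} sets baseline at 0600 on day 1, so the word in the exclusion must mean an earlier run-in sample.

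**1. Does the hourly limit close the gap?** Over 24 h, 0.5 mmol/L/h is 0.5 × 24 = 12 mmol/L. Rises of 8 and 10 mmol/L over 24 h are 8/24 = 0.33 and 10/24 = 0.42 mmol/L/h, both below 0.5. The hourly limit removes a rise of 8 only if it took under 8/0.5 = 16 h, and a rise of 10 only if it took under 10/0.5 = 20 h. Slower rises within 24 h remain eligible.

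**2. Example: 118 to 127 mmol/L in 24 h.** Rise 127 − 118 = 9; rate 9/24 = 0.375 mmol/L/h.

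| Check | Day 1 | Day 2 or 3 |
|---|---|---|
| Sodium 127 | within 115–130 | not above 134 |
| Limit on 24 h rise | 10, passed | 8, exceeded |
| Limit on hourly rise | 0.5, passed | none |
| Result | 7.5 mg or 1000 mL | no treatment, either arm |

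**3. Who falls in the gap?** Starting sodium is the day-1 value minus the rise. The upper bound is below 130 − 8 = 122 mmol/L. The lower bound is 115 − 10 = 105 mmol/L if the 115–130 range is read on day 1 only.

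**4. Do the Table 2 triggers count the earlier rise?** They run from the dose. To see how much this matters, assume a rolling 24 h window that reaches into the run-in (the protocol does not say how the window is read), a linear prior rise r up to 0600, a dose at 1000, and sodium either flat or still rising at the same rate from 0600 to 1000. The post-dose rise that brings the 24 h total to 10 is then:

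- 6 h sample (1600): flat 10 − 14r/24; still rising 10 − 18r/24
- 12 h sample (2200): flat 10 − 8r/24; still rising 10 − 12r/24

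| Prior rise r | 6 h, flat / rising | 12 h, flat / rising |
|---|---|---|
| 8 | 5.33 / 4.00 | 7.33 / 6.00 |
| 9 | 4.75 / 3.25 | 7.00 / 5.50 |
| 10 | 4.17 / 2.50 | 6.67 / 5.00 |
| Table 2 acts above | 6 | 8 |

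All entries lie below the trigger, so the total could pass 10 before Table 2's 6 h and 12 h triggers act.

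**5. How much of that comes from 8 versus 10?** The 6 h figure falls below 6 once r > 4 × 24/14 = 6.86 (flat) or 4 × 24/18 = 5.33 (rising). The 12 h figure falls below 8 once r > 2 × 24/8 = 6.00 or 2 × 24/12 = 4.00. So the shortfall opens at prior rises well under 8. Lowering the day-1 limit from 10 to 8 improves the worst case by 14 × 2/24 = 1.17 or 18 × 2/24 = 1.50 mmol/L at 6 h, and by 8 × 2/24 = 0.67 or 12 × 2/24 = 1.00 mmol/L at 12 h. Most of the shortfall comes from Table 2 counting from the dose.

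**The case against.** **The two limits do different jobs.** Ten is the guideline ceiling cited in the Background and the protocol's definition of overcorrection. Eight is the top of the titration target, applied after a treatment has been given. It is true that 10 has a source and is not a slip. But the > 8 rule also stops fluid restriction, and the eligibility list itself treats a pre-study rise as a demyelination risk, so the difference still needs a reason.

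**Footnote b may already cover day 1.** Its wording names no day, whereas footnote a is confined to days 2 and 3. However, its marker appears only on the day-2 and day-3 rows, and the text places the review of the increment at visits after the first. If day 1 was intended, the table should say so.

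**The run-in or the treating team would remove these patients.** They may. The autocorrection exclusion carries no number in this article, and the team's power to withdraw a participant is discretionary. Neither does so reliably.

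**A reader might infer that nothing later takes the earlier rise into account.** The document does not support that. The overcorrection rule in {11b} is not tied to dose time, and tolvaptan recipients have sodium measured at 6 and 12 h after the dose, so a combined rise above 10 mmol/L could be seen and managed. What stands is narrower: the earlier, preventive triggers in Table 2 count only the post-dose rise. A fluid-restriction participant now above 125 mmol/L has bloods every 12 h.

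**Conclusion.** The inconsistency holds. A 24 h rise above 8 and up to 10 mmol/L leads to treatment on day 1 and to no treatment on days 2 and 3, and the hourly limit does not close that window. Those affected all started below 122 mmol/L.

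The point is a cheap safety improvement, and its size is limited. The number affected cannot be known from the document. Purely for scale, an assumed 1% to 5% would be about 2 to 8 of the 166 planned participants (1.7 to 8.3), of whom about 1 to 4 of 83 would be on tolvaptan.

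Two stronger readings should be avoided. A reader might infer a bias between arms, but the day-1 rule is the same in both. A reader might also take the headroom figures as the harm caused by using 10 instead of 8. They rest on the assumed window, linear rise and dose time, and they mainly reflect Table 2's clock, which is a separate limitation.

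**What to change.** Fill the empty day-1 increment cell of Table 1:

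- At a prior 24 h increment of 8 mmol/L or less, start 7.5 mg or 1000 mL as now.
- Above 8 mmol/L, defer randomisation and the first dose to the next morning. Then recheck the increment and the 115–130 mmol/L criterion.

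Keep the limits of 10 mmol/L/24 h and 0.5 mmol/L/h as outright exclusions, and say which run-in sample baseline means there. The deferral must come before the envelope is opened, so that allocation stays concealed and both arms are handled alike. If the clinical team and the DSMB prefer to treat after a rise of more than 8 and up to 10 mmol/L on day 1, the protocol should say why that is acceptable then and not on days 2 and 3.

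The cost is an amendment to one table row plus a deferral step in the enrolment procedure. The sodium values come from routine care. A few patients would start either treatment a day later, or would autocorrect above 130 mmol/L and drop out of eligibility. The change aligns day 1 with days 2 and 3. It does not alter the fact that Table 2 counts only from the dose.
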